### Statistical considerations

Given the novel nature of ASTuTE, it is not possible to estimate the event rate for the primary endpoint proportion change in shared decision making regarding use of ADT. If an incorrect estimate is used, there is a risk of underpowering the study. Therefore, an interim analysis will be performed at 200 participants. This will allow for early assessment into the rates of management change and help determine the final number of participants needed to adequately power the final analysis of the study. At this time, 800 participants are planned for enrolment, with final numbers to be determined at the time of the interim analysis.

The McNemar’s test will be used to analyse the primary endpoint. There is a rare chance that the number of pre- to post-test recommendations of Yes-No and No-Yes is equal. This could lead to the null hypothesis being retained when the ArteraAI Prostate test is actually outperforming standard of care. As such, the study is designed to be hypothesis-generating, rather than focusing on a specific hypothesis that would define the sample size. This trial of implementation which assesses rates of management change based on a biomarker test has been used in recent literature. The DCISionRT^®^ study, used this approach to assess a breast genomic biomarker impact on radiation therapy recommendations [24].

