### Endpoints

The primary objective is to assess the impact of the ArteraAI Prostate Test on shared ST-ADT decisions with IR prostate cancer men undergoing curative radiotherapy. To evaluate this, the endpoints of shared ST-ADT decisions pre-test and post-test will be recorded. The primary endpoint is the percentage of cases with changes in ST-ADT shared decision recommendations.

The secondary objectives will be assessed through linkage with the Prostate Cancer Outcomes Registry (PCOR) and will assess efficacy and quality of life. The secondary endpoint of efficacy will be assessed at 5 years using the Phoenix criteria of PSA nadir + 2ng/mL [21], and/or initiation of salvage treatment and/or imaging confirming recurrent disease. The secondary endpoint of quality of life will be assessed using the Expanded Prostate Cancer Index Composite questionnaire (EPIC-26).

The primary hypothesis is that the ArteraAI Prostate Test will result in changes to ADT management of IR prostate cancer patients. The secondary hypotheses are that this will be accompanied by ongoing high rates of disease control and improved quality of life for those spared ADT.

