**Fig. 4 Fig4:**
[figure not shown]
2 × 2 contingency table illustrating McNemar’s test for paired data to assess rates of change for the biomarker test, ArteraAI Prostate Test, on shared ADT decision making. Primary endpoint of proportion changing shared decision on use of ADT is calculated as (b + c) / (a + b + c + d)

Multivariate logistic regression analyses will also be used to assess the odds ratios (OR) of factors leading to the pre-test and the post-test ADT recommendations. Pre-test exploratory covariates can include age, ISUP grade, initial PSA, tumour stage and percentage of cores positive. Post-test covariates will also include the ArteraAI Prostate test results.

The study opened to enrolment in December 2023, and is expected to complete accrual in 2025.

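### McNemar's test is attached to a primary endpoint of total change, but it tests only the net shift in ADT recommendations and can fail whenever the two directions are similar in number, not only at an exact tie

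*Protocol article*

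**What the plan says.** Endpoints (Protocol article): "The primary endpoint is the percentage of cases with changes in ST-ADT shared decision recommendations". The Fig. 4 caption gives the same quantity as a formula, "calculated as (b + c) / (a + b + c + d" (closing bracket cut), so both discordant cells are added. The hypothesis has no direction: "The primary hypothesis is that the ArteraAI Prostate Test will result in changes to ADT management of IR prostate cancer patients".

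Statistical considerations then states: "The McNemar’s test will be used to analyse the primary endpoint". It admits one weakness, "There is a rare chance that the number of pre- to post-test recommendations of Yes-No and No-Yes is equal", and draws this consequence: "This could lead to the null hypothesis being retained when the ArteraAI Prostate test is actually outperforming standard of care". On those grounds it calls the study hypothesis-generating and keeps the test.

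On size, "800 participants are planned for enrolment, with final numbers to be determined at the time of the interim analysis". The interim look at 200 patients is to assess how often management changes and to help set the number that gives the final analysis adequate power. No alpha, power, expected change rate or expected split between the two directions is given.

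The Data analysis plan also promises rates of change with confidence intervals, and the Methods part of the Abstract pairs McNemar's test with descriptive statistics.

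**The concern.** Let b be the Yes-to-No changes, c the No-to-Yes changes and N all patients. The endpoint is the sum (b+c)/N. McNemar's null hypothesis is b = c in expectation, meaning no net shift in the proportion recommended ADT. These are different questions. A biomarker that moves many men off ADT and about as many onto it scores high on the endpoint and shows nothing on the test. One that moves few men, nearly all one way, does the reverse.

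Three things follow:

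- The p-value beside the primary endpoint does not test the primary hypothesis.
- The stated limitation understates when the test fails, because it covers only an exact tie.
- The observed change rate alone cannot size the final analysis if that analysis is McNemar's test, because its power also depends on the split between b and c.

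**Working it through.** **Inputs.** From the documents: N=800 (Statistical considerations), the endpoint formula (Fig. 4 caption), and 42% overall change with 46% Yes-to-No and 35% No-to-Yes in the breast biomarker study (Discussion). Assumed: two-sided alpha 0.05, the pre-test Yes share y, and a 4% change rate as the low example. The planned 800 cannot be reproduced, because no inputs to it are stated.

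**Reading of 46% and 35%.** They do not sum to 42% or to 100%, so they are taken as rates within the pre-test Yes and No groups. Then 0.46y + 0.35(1−y) = 0.42 gives y = 0.07/0.11 = 0.636.

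**Step 1: hold the switch rates, vary the Yes share.** With p = 0.46y and q = 0.35(1−y), total change is s = p+q and net shift is d = p−q. Asymptotic McNemar power is Φ[(|d|√N − 1.96√s)/√(s−d²)] plus the opposite tail. At N=800:

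| y | p | q | total change s | net shift d | power |
|---|---|---|---|---|---|
| 0.60 | 0.276 | 0.140 | 41.6% | 13.6% | about 100% |
| 0.50 | 0.230 | 0.175 | 40.5% | 5.5% | 69% |
| 0.48 | 0.221 | 0.182 | 40.3% | 3.9% | 41% |
| 0.45 | 0.207 | 0.193 | 40.0% | 1.5% | 10% |
| 0.43 | 0.198 | 0.200 | 39.7% | −0.2% | 5% |

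The flows balance at y = 0.35/0.81 = 0.432. Across the table the endpoint moves by about two percentage points and the power runs from about 100% down to the alpha level. Simulation of the uncorrected chi-square at y = 0.50, 0.45 and 0.432 gave 68.7%, 10.0% and 5.0%.

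**Step 2: a tie is the wrong event.** Take 320 changes (40% of 800) with a true 50:50 split. The probability of an exact 160:160 tie is 4.5%; the probability of not rejecting is about 95%. A split of 170:150 gives exact p=0.288.

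**Step 3: where significance starts.** Take 336 changes (42% of 800). The chi-square is (b−c)²/(b+c).

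- 185:151: 34²/336 = 3.44, p=0.064; exact p=0.072.
- 186:150: 36²/336 = 3.86, p=0.0495; exact p=0.056.
- 187:149: 38²/336 = 4.30, p=0.038; exact p=0.043.

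So the exact test is non-significant up to 186:150, and the uncorrected chi-square up to 185:151.

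**Step 4: the reverse case.** 32 changes in 800 is 4%. A split of 24:8 gives exact p=0.007.

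**Step 5: sizing.** Fix the change rate at 40% and N at 800. Simulated rejection is 5% at a 50:50 split, 43% at 55:45 and 95% at 60:40. One change rate is compatible with almost any power.

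**Step 6: the endpoint itself.** Exact 95% intervals at N=800 are 36.6-43.5% for 320/800 and 2.8-5.6% for 32/800. At the interim, 80/200 gives 33.2-47.1%. These intervals do not depend on direction.

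**The case against.** The strongest reply is that most of the right analysis is already planned. The endpoint is correctly defined, the Data analysis plan promises change rates with confidence intervals, the study is labelled hypothesis-generating, and no success rule hangs on the McNemar p-value. Net ADT use is also a legitimate paired question. All of this stands, and it lowers the severity. It does not remove the mismatch, because the text still names McNemar's test as the analysis of the primary endpoint and still speaks of powering the final analysis.

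Four stronger readings are tempting, and the documents do not support them:

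- **That near-balance is likely.** Neither the pre-test Yes share nor the share of biomarker-positive men is given. The secondary hypothesis looks to men spared ADT, and the cited precedent implies about 64% Yes, where power is close to 100%. The low-power rows show what can happen, not what is expected.
- **That a non-significant result would be reported as no impact.** The protocol itself warns that the null may be retained despite a real effect, and the change rate would stand beside the p-value.
- **That McNemar's test has nothing to do with b+c.** The sum is the denominator of the statistic. The accurate statement is that the test does not test the sum.
- **That the interim cannot inform sizing.** Its paired table will show the split as well. The fault is that the text names only the change rate as the basis.

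**Conclusion.** The point holds as a mismatch between test and endpoint, a misdescribed limitation and an incomplete basis for re-sizing. Severity is should-fix. With the quoted switch rates at N=800, power runs from about 100% to 5% while total change stays near 40%, and a 4% change rate can be significant if the changes are clearly one-sided. This rests on two-sided alpha 0.05, an assumed pre-test Yes share and borrowed switch rates; the 4% is illustrative. The mismatch itself needs none of these, since it follows from the formula in the Fig. 4 caption and McNemar's null hypothesis.

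The remark that the test may be doing better than usual care is a separate error of wording. A change between pre-test and post-test decisions cannot show that the new decisions are better.

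**What to change.** - Name the estimate of (b+c)/N with its 95% confidence interval, already planned, as the primary analysis. Report the Yes-to-No and No-to-Yes rates beside it.
- Base the re-sizing at 200 patients on the precision of that interval. For reference, 40% at N=800 gives 36.6-43.5%.
- Keep McNemar's test as a labelled secondary analysis of the net shift in ADT recommendation, optionally within biomarker-positive and biomarker-negative men. Amend the Fig. 4 caption, which presents the test as a measure of rates of change.
- Reword the sentence on the tie to say that the test loses power whenever the two directions are similar in number, and remove the claim of superiority over standard care.

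The cost is wording in the protocol and the analysis plan, with no new data. The trial gives up a headline p-value for its primary endpoint.

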### Data analysis plan

Simple statistical analysis will be performed by calculating “rates of change” with appropriate confidence intervals for changes in pre- and post-testing treatment recommendations. Summary statistics will be used to present the treatment recommendation pre- and post- incorporation of test results and secondary analyses.

For instance, in order to assess the impact of ArteraAI Prostate Test results on recommendations for shared ST-ADT use, the percentage change in recommendations will be calculated, and McNemar’s test for paired data will be used to assess the change in shared ST-ADT recommendations pre-test versus post-test, Fig. 4.

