## Design

The ASTuTE trial (*A*rtificial intelligence *S*teering *T*estosterone deprivation *T*reatments in prostate cancer *E*xternal-beam radiotherapy) is an open-label, multicentre, prospective registry and trial of implementation that aims to collect real world data on the use of a MMAI-driven biomarker digital histopathology test developed by Artera^®^ for use in IR prostate cancer men undergoing curative radiotherapy.

The trial was designed by the authors, using the SPIRIT-AI extension recommendations [16], and was devised to assess the impact of the ArteraAI Prostate Test on shared ST-ADT decisions. The trial was first registered with the Australian Clinical Trials Registry (ACTRN12623000713695) on 5 July 2023. Central ethical approval was obtained from St Vincent’s Human Research Ethics Committee (HREC 2023/ETH01630) in 2023, with the first patient enrolled December 2023. Local ethical and governance approval has been obtained from all participating sites. The study is being conducted in accordance with the Declaration of Helsinki, the National Health and Medical Research Council (NHMRC) National Statement on Ethical Conduct in Human Research 2007 and the NHMRC Australian Code for Responsible Conduct of Research. All participants are providing written informed consent.

The primary goal of this study is to create a de-identified database of patients, test results, and treatment decisions that can be queried to determine the clinical utility of the MMAI digital histopathology test known as ArteraAI Prostate Test, in the utilisation of ST-ADT for men with IR prostate cancer. Eligible participants will undergo data collection as per Fig. 2. For patients that will receive radiotherapy, all curative intent radiotherapy dose/fractionation schedules are allowed including conventional [17], moderately hypofractionated [18] and ultra-hypofractioned [19] as well as dominant intraprostatic lesion (DIL) boosting [20]; this will enable data generalizability across modern techniques.

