**Fig. 3 Fig3:**
[figure not shown]
**a and b.** ArteraAI Prostate Test report examples. Green box highlighting the prognostic model score and Blue box highlighting the predictive model result for ADT benefit

**Table 2 Tab2:** Schedule of assessments (according to SPIRIT-AI extension)

	Enrolment / Pre-test^1^	Post-test^2^	5-year follow-up
1. Demographics	X		
2. Prostate cancer history	X		
3. Shared ADT decision recommendation as determined by primary clinician and participant	X	X	
4. EPIC-26 Quality of Life questionnaire	X^*3*^		X^*3*^
5. Disease Control			X^*3*^

^*1*^
*Enrolment / pre-test can happen over a period of 14 days*

^*2*^
*Post-test data collection may occur at initial consult if ArteraAI Prostate Test results are available*

^*3*^
*Data linkage through Prostate Cancer Outcomes Registry at median 5-year follow-up.*

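### The quality-of-life hypothesis is comparative, but the only method named for the secondary analyses is summary statistics, which cannot answer it in a non-randomised cohort

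*Protocol article*

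**What the plan says.** All statements are in the protocol article.

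- **Hypothesis (Endpoints).** The secondary hypotheses expect "ongoing high rates of disease control and improved quality of life for those spared ADT". No comparator is named.
- **Instrument (Endpoints).** "The secondary endpoint of quality of life will be assessed using the Expanded Prostate Cancer Index Composite questionnaire (EPIC-26").
- **Timing (Table 2).** EPIC-26 is marked at enrolment/pre-test and at 5 years, and nowhere between. Both entries carry the footnote "Data linkage through Prostate Cancer Outcomes Registry at median 5-year follow-up".
- **Method (Data analysis plan).** "Summary statistics will be used to present the treatment recommendation pre- and post- incorporation of test results and secondary analyses".
- **Modelling (text after Fig. 4).** "Multivariate logistic regression analyses will also be used to assess the odds ratios (OR) of factors leading to the pre-test and the post-test ADT recommendations". The covariates listed are age, ISUP grade, PSA, stage and percentage of positive cores, plus the test result for the post-test model. No model is tied to EPIC-26.
- **Design.** The study is an "open-label, multicentre, prospective registry and trial of implementation". Planned curative radiotherapy is an inclusion criterion for every man (Table 1).

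**The concern.** To say that quality of life is improved in men spared ADT is to compare them with men given ADT, or with the same men had they received it. A summary of EPIC-26 scores makes neither comparison fairly.

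- The change from baseline within spared men includes the effects of radiotherapy and about five years of ageing. It can fall even if sparing ADT helped.
- The 5-year difference between spared and treated men includes whatever separated them at baseline. They are not exchangeable: the article's own regression looks for age, tumour features and the test result as drivers of the decision.
- The difference in change scores can err in the opposite direction if a baseline gap shrinks over time.

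If the plan is followed as written, the sign of the reported quality-of-life result could depend on which summary is shown. The baseline score that would support a better contrast is already scheduled.

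**Working it through.** The article gives no EPIC-26 effect size, SD, correlation or power, so there is no figure of its own to reproduce. The two calculations below are illustrations.

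**1. Closed-form illustration**

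*Group sizes.* The Discussion reports a breast biomarker implementation study with 42% changed overall, 46% Yes-to-No and 35% No-to-Yes. If p is the pre-test Yes share, 0.46p + 0.35(1 − p) = 0.42, so p = 0.07/0.11 = 0.636. Applied to the 800 planned men, this gives 509 with pre-test Yes: 234 changing to No and 275 staying at Yes. Borrowing these rates, and complete scores for all men, are assumptions.

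*Other assumptions.* Domain SD 20, correlation r = 0.6 between baseline and 5 years, spared men 5 points higher at baseline, no true ADT effect.

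*Standard errors*
- Unadjusted 5-year difference: 20 × √(1/234 + 1/275) = 1.78
- Difference in change scores: 1.78 × √(2(1 − 0.6)) = 1.59
- ANCOVA on baseline score only: 1.78 × √(1 − 0.36) = 1.42

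*Expected estimate when the truth is zero*

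| Contrast | Gap shrinks by factor r | Gap stable over time |
|---|---|---|
| Unadjusted 5-year | 0.6 × 5 = +3.0 | +5.0 |
| Change score | −(1 − 0.6) × 5 = −2.0 | 0 |
| ANCOVA | 0 | 5 − 0.6 × 5 = +2.0 |

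In the first column, for r from 0.4 to 0.7, the unadjusted bias runs from +2.0 to +3.5 and the change-score bias from −3.0 to −1.5. ANCOVA on baseline then has r², or 16% to 49%, less variance than the unadjusted 5-year contrast.

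**2. Simulation under different assumptions**

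1,000 cohorts of 800 men; SD 15; correlation parameter 0.6; common drift −5; any benefit of sparing added to the spared men's 5-year score. Being spared depends on baseline score (log-odds −0.5, 0 or +0.5 per SD) and, in proportion, on age. The three values in each cell follow that order.

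| True benefit | Unadjusted 5-year difference | Change in spared men | Adjusted for baseline and age |
|---|---|---|---|
| 0 | −5.1 / 0.0 / +5.1 | −3.8 / −5.0 / −6.2 | 0.0 / 0.0 / 0.0 |
| 2 | −3.1 / 2.0 / +7.1 | −1.8 / −3.0 / −4.2 | 2.0 / 2.0 / 2.0 |
| 4 | −1.1 / 4.1 / +9.1 | +0.2 / −0.9 / −2.2 | 4.0 / 4.1 / 4.1 |

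The unadjusted difference shows harm where sparing helps, or benefit where there is none, depending on selection. The change in spared men is negative in 8 of 9 scenarios although sparing never harms. The adjusted contrast recovers the truth, but only because every confounder is measured in the simulation.

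**3. Precision with a further covariate**

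The SE of 1.42 applies to adjustment for baseline alone. If the covariates explain 36% of the variance in the decision and add little about EPIC-26, the SE becomes 1.42/√0.64 = 1.78, the unadjusted value. At 50% it is 1.42/√0.50 = 2.01. The ArteraAI result is the covariate most likely to have this effect, since it is meant to drive the post-test decision.

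**The case against.** **The sentence concerns presentation and is not exclusive.** This stands. It also covers the pre- and post-test recommendations, which nevertheless receive confidence intervals, McNemar's test and logistic regression. A reader might infer that the plan prescribes raw EPIC-26 summaries and rules out adjustment. The text supports neither: it does not call the summaries raw, and baseline scores are scheduled, so change scores are possible. The full protocol or analysis plan, not shown, may hold a model. What remains is that the article states a comparative hypothesis, names one method for the secondary analyses, and that method cannot answer it. That is a mismatch between two statements rather than a gap.

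**The sizes follow from their assumptions.** This also stands. SD, correlation, imbalance and group split are all assumed. A reader might further infer that ANCOVA is the unbiased answer. It is not in general: if the baseline gap is stable, the change score is right and ANCOVA shows a false +2.0. This limits what the adjusted estimate may be called and argues for showing both contrasts.

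**Full adjustment may cost precision.** Correct where the ArteraAI result is a covariate, so it should not be in the main model.

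**The study is hypothesis-generating.** Statistical considerations attaches that label to McNemar's test and the sample size. It lowers the stakes but does not make a summary answer a comparative question.

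**Conclusion.** The point holds in a limited form. The quality-of-life hypothesis is comparative, allocation is not randomised, and the only named method for the secondary analyses is descriptive. Unadjusted EPIC-26 summaries cannot answer the hypothesis and, under plausible assumptions, can have the wrong sign. In the illustration with no true effect, two natural summaries give +3.0 and −2.0 points.

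These sizes rest wholly on assumed inputs. They show that the sign can be wrong, not that it will be. Nor can baseline adjustment be relied on to remove all bias; that requires selection to act through measured variables. The primary endpoint and sample size are not affected. This is a cheap improvement.

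**What to change.** In the Data analysis plan:

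1. Keep summary statistics as the descriptive display of EPIC-26.
2. Name the comparator for the quality-of-life hypothesis, for example post-test No versus Yes among men whose pre-test decision was Yes.
3. Report the difference in 5-year EPIC-26 domain scores, adjusted for the baseline score of that domain, age and the recorded tumour features (ISUP grade, PSA, T-stage, percentage of positive cores), with a 95% CI, and describe it as an association.
4. Show the difference in change scores as a sensitivity analysis, because the adjusted and change-score contrasts rest on different assumptions about the baseline gap.
5. Add the ArteraAI result only as a sensitivity covariate, because it drives the decision and can inflate the standard error.

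Alternatively, restate the quality-of-life objective as descriptive and drop the claim of improvement.

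The cost is a sentence or two in the plan and one regression per EPIC-26 domain, using variables already scheduled or recorded. The drawbacks are a little more analysis work, loss or imputation of men without a baseline score, and residual confounding that no adjustment for recorded variables removes.

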**Discussion:**

ASTuTE will determine the impact of a novel prognostic and predictive biomarker on shared decision-making in the short term, and both quality of life and disease control in the medium term. If the biomarker demonstrates a significant impact on treatment decisions, it could lead to more personalized treatment strategies for men with intermediate-risk prostate cancer, potentially reducing overtreatment and improving quality of life. A potential limitation is the variability in clinical practice across different centers inherent in real-world studies.

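### The named primary test and the logistic models treat patients as independent, although the treating clinician co-determines each decision and practice is expected to vary between centres

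*Protocol article*

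**What the plan says.** The primary endpoint is the share of participants whose shared ST-ADT decision changes. The legend of Fig. 4 defines it as (b + c)/(a + b + c + d), from a single table that pools all participants.

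- **Test.** Statistical considerations and the Data analysis plan both name McNemar's test. The latter says that "McNemar’s test for paired data will be used to assess the change in shared ST-ADT recommendations pre-test versus post-test".
- **Interval.** The Data analysis plan promises appropriate confidence intervals for the rates of change, under the label of simple statistical analysis. It names no method and gives no width.
- **Regression.** The text after Fig. 4 plans logistic models for the pre-test and post-test recommendations. The covariates listed are patient and tumour factors, plus the test result in the post-test model.
- **Who decides.** Table 2 lists the outcome as "Shared ADT decision recommendation as determined by primary clinician and participant".
- **Variation.** The Discussion part of the abstract says: "A potential limitation is the variability in clinical practice across different centers inherent in real-world studies".
- **Size.** Statistical considerations states: "At this time, 800 participants are planned for enrolment, with final numbers to be determined at the time of the interim analysis". It also says that "an interim analysis will be performed at 200 participants", and that "it is not possible to estimate the event rate for the primary endpoint proportion change in shared decision making regarding use of ADT".

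**The concern.** The ordinary McNemar test assumes that the patient pairs are independent of one another, and so does a simple binomial interval. Here the endpoint is itself a decision, and one of the two people making it may do so for many patients. Variation in practice therefore acts directly on the measured outcome. The article names a source of correlation, then names methods that take no account of it.

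Two mechanisms need to be kept apart:

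- **Frequency.** Clinicians may differ in how often they change a decision after seeing the test. This widens the true uncertainty of the change rate.
- **Direction.** Clinicians may differ in which way their changes go. One who usually recommends ADT before the test can contribute mainly Yes-No changes, and one who usually withholds it mainly No-Yes. This is what disturbs McNemar's test.

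At stake is how precisely the trial's main result is reported. The interim analysis also matters: a final sample size derived from it under independence would be too small if clustering is present.

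**Working it through.** **No planning figure to reproduce.** The article gives 800 as a provisional number, with no alpha, power, target precision or assumed change rate. The 800 therefore cannot be rebuilt, and no stated interval can be checked.

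**Inputs.** N = 800 (Statistical considerations). Change rate p = 0.42, borrowed for illustration from the breast biomarker study described in the article's Discussion; it is not a planning value. Number of clinicians K = 20 to 80, of equal size, and ICC = 0 to 0.10: both are assumptions, because the article gives neither.

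**Step 1, independence.** Half-width = 1.96 × √(p(1 − p)/N) = 1.96 × √(0.42 × 0.58/800) = 3.42 points. At N = 200 it is 6.84 points.

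**Step 2, clustering.** With m = 800/K patients per clinician, the design effect is DE = 1 + (m − 1) × ICC, the effective N is 800/DE, and the half-width is 3.42 × √DE.

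| Clinicians × patients | ICC | DE | Effective N | Half-width (points) |
|---|---|---|---|---|
| any | 0 | 1.00 | 800 | 3.42 |
| 80 × 10 | 0.02 | 1.18 | 678 | 3.72 |
| 80 × 10 | 0.10 | 1.90 | 421 | 4.71 |
| 40 × 20 | 0.02 | 1.38 | 580 | 4.02 |
| 40 × 20 | 0.05 | 1.95 | 410 | 4.78 |
| 40 × 20 | 0.10 | 2.90 | 276 | 5.82 |
| 20 × 40 | 0.05 | 2.95 | 271 | 5.87 |
| 20 × 40 | 0.10 | 4.90 | 163 | 7.57 |

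**Step 3, coverage of the simple interval.** Beta-binomial simulation, 20,000 runs, 40 × 20. The nominal 95% interval covers 94.8% at ICC 0, 90.5% at 0.02, 83.2% at 0.05 and 74.3% at 0.10. With 80 × 10 at ICC 0.02 it covers 92.6%.

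**Step 4, McNemar's test under its null (b and c equal in expectation).**

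- Clinicians differ only in how often they change: type I error stays between 4.6% and 5.2% in every scenario.
- Direction also varies by clinician, with the same ICC: 40 × 20 gives 7.2%, 10.1% and 15.4% at ICC 0.02, 0.05 and 0.10.
- Only the pre-test ADT rate varies by clinician, with change probabilities of 46% Yes-No and 35% No-Yes (the breast study again). Equal b and c then need a mean pre-test Yes share of 0.35/(0.46 + 0.35) = 43.2%. Type I error with 40 × 20 is about 7%, 9% to 10% and 14% at ICC 0.02, 0.05 and 0.10. With 20 × 40 it is about 9%, 14% and 22%, and with 80 × 10 about 6%, 7% and 9% to 10%.

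**Step 5, the interim.** With the same 40 clinicians, 200 participants means m = 5. At ICC 0.05, DE is 1 + 4 × 0.05 = 1.20 at the interim, against 1 + 19 × 0.05 = 1.95 at 800. The ICC can be carried forward from the interim; the interim design effect cannot.

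**The case against.** **The article states no error bars.** A reader might infer that stated intervals are too narrow. That is not supported: no interval or width appears, and appropriate confidence intervals could include a cluster-robust one. This stands, so the point bears most on the test and the logistic models, and on the interval only if a simple binomial method is used.

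**A small group of clinicians is not documented.** The article says only that there are multiple centres. Nor does it show that site and clinician go unrecorded, since Table 2 is a high-level schedule. Both stand. With 80 clinicians and ICC 0.02 the half-width moves only from 3.42 to 3.72 points, and at ICC 0 nothing changes. The regression covariates are also an open list.

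**McNemar's p-values are not necessarily too small.** This stands. Step 4 shows no inflation when only the frequency of change clusters.

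**The simple interval may be adequate for the clinicians who took part.** Under-coverage arises when inference extends to other clinicians. That is true, but a trial meant to show a test's utility in real-world practice plainly aims beyond its own participants.

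**The variance method usually belongs in the statistical analysis plan, and the article says that "the study is designed to be hypothesis-generating, rather than focusing on a specific hypothesis that would define the sample size".** Both lower the severity. Neither removes the point: the article does not leave the primary test open but names one that assumes independence. The change rate and its interval are also the trial's main product, and the interim is to use the observed change rate to set the final size.

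**Conclusion.** The point holds in a conditional form. The named McNemar test on a pooled table, and the logistic models as described, treat patients as independent in a setting where the article itself gives reason to doubt it. If changes correlate within clinician or centre, a simple binomial interval would be too narrow for wider inference. McNemar's test would reject too often only if direction clusters too, for example because pre-test ADT use differs by clinician. The point estimate (b + c)/N is the same whichever variance method is used.

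The size cannot be established from the article. Under the assumptions above, the 95% half-width lies between 3.4 points (ICC 0) and 7.6 points (20 clinicians, ICC 0.10), with 4.8 points for 40 clinicians at ICC 0.05. No stated figure is contradicted. This is a low-severity improvement, worth making because it is cheap.

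**What to change.** Use recorded site and treating clinician as the cluster (clinician within site), and then:

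- report the change rate with a cluster-robust interval that has a small-sample correction;
- replace the ordinary McNemar test with a clustered-pair version (Durkalski or Obuchowski) or a GEE;
- apply the same clustering to the pre-test and post-test logistic models;
- at 200 participants, estimate the ICC and project the design effect to the cluster sizes expected at the final number. An ICC from 200 participants will be imprecise, so show a range.

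The cost is some wording in the analysis plan, a little more analysis work, and somewhat wider intervals if clustering is present. If site and clinician are not already captured, it also needs those two identifiers. No patient procedure changes.
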